## Abstract

**Background:**

Probiotics may be an ideal choice for these patients, given it can improve the defecation and quality of life of individuals with chronic diarrhoea. However, evidence-based medical research is still limited to support its use as a diarrhoea agent.

**Method:**

A randomized, double-blind, placebo-controlled clinical trial is designed to pinpoint the efficiency and possible action modes of probiotics for chronic diarrhoea. 200 eligible volunteers with chronic diarrhoea are randomly assigned to a probiotic group (orally taking *Lactobacillus plantarum* p9 probiotics powder) or a placebo group. Except an independent project administrator who will be responsible for unblinding, the other researchers are blinded. Primary outcome is diarrhoea severity score, and secondary outcomes include weekly mean frequency of defecation, weekly mean stool appearance score, weekly mean stool urgency score, emotional state score, gut microbiome, and faecal metabolome. Each outcome measure will be assessed at the timepoints of pre-administration (day 0), administration (day 14 and/or 28), and post-administration (day 42) to identity inter- and intra-groups differences. Adverse events will be recorded to evaluate the safety of *L. plantarum* p9.

**Discussion:**

The study protocol will provide high-quality evidence for the use of probiotics as a diarrhoea agent when it is strictly conducted out, providing evidence regarding whether and to what extent *L. plantarum* p9 can improve the defecation and well-being of individuals with chronic diarrhoea.

**Trial registration:**

Chinese Clinical Trial Registry (ChiCTR) (NO. ChiCTR2000038410). Registered on November 22, 2020, https://www.chictr.org.cn/showproj.aspx?proj=56542.

## Background

1

Diarrhoea is defined as the situation that the stool weight is more than 200 g per 24 h containing more than 200 ml fluid per 24 h, or the times of defecating loose stools are greater than 3 within 24 h [[1], [2], [3]]. And an individual can be diagnosed as chronic diarrhoea when diarrhoea lasts more than 4 weeks [4,5]. The prevalence of chronic diarrhoea is estimated to be 3–5% among general population [6,7] and 9.6–14.2% in the elderly (aged more than 60) [8,9]. It may disturb the patient's quality of life, work performance and well-being as well as increase their medical expenses [10], and the chronic diarrhoea-related economical loss just from work-loss is estimated to be approximate $350, 000, 000 annually [11].

Probiotics always hold the advantages of safety and widely public acceptance [[27], [28], [29]]. Evidence has showed that probiotics are safe for the study volunteers across the whole age spectrum, only with caution advised in immunologically vulnerable populations [27], and without significantly side effects when used in the long-term for chronic diarrhoea [26]. However, data on the effectiveness of probiotics in the treatment of chronic diarrhoea is still lacking and limited to anecdotal experience shared by people [26,30] or case reports [31] which suggest that probiotics may offer a way to bring about resolution in chronic diarrhoea [26,30,31]. Thus, a study protocol for high-level evidence is warrant for the efficacy and safety of probiotics in individuals’ chronic diarrhoea.

## Methods and design

2

### Design

2.1

This study is a randomized, double-blind, placebo-controlled clinical trial, implemented in Nanchang city, Jiangxi province, China. Volunteers can orally intake *L. plantarum* p9 or placebo at home and are followed up online via completing designed online questionnaires. For the stool sample collection, volunteers are required to immediately inform researchers as soon as prepared according to instructions, and the researchers timely take it back for further detection. This paper is written according to the Standard Protocol Items: Recommendations for Interventional Trials (SPIRIT) [32]. The flow chart of the study is presented as Fig. 1.

**Fig. 1 fig1:**
[figure not shown]
Flow chart of the protocol.

### Inclusion criteria

2.2

Eligible volunteers should have diarrhoea onset for at least 6 months before enrolment, with loose or watery stool (looked like Bristol type 5, 6, or 7 (Appendix 1) [33]) at least 25% of the times of defecation within the past 3 months. The volunteers involved in this study will be patients with chronic diarrhoea aged 18–65 years. For patients aged from 18 (exclusive) to 50 (inclusive) years, the result of stool test (including occult blood) conducted during the screening period is normal or is abnormal but is judged by the investigators as clinically irrelevant. For patients aged from 50 (exclusive) to 65 (inclusive) years, the result of colonoscopy performed at a tertiary or higher-level hospital within the past 6 months is normal or is abnormal but must be judged by the investigators as clinically irrelevant. Of course, the volunteers should be willing to sign the informed consent form, and only the written informed consent form is provided can then the volunteer participates in the trials.

### Exclusion criteria

2.3

Volunteers have one of the following situations are excluded.(1)Personal or family history of colon cancer, celiac disease, or inflammatory bowel disease.(2)Confirmed Intestinal organic diseases by colonoscopy.(3)Plans to be pregnant with or father a child in near future, or at the status of pregnancy or breastfeeding in women.(4)Allergies to L. *plantarum* p9 or placebo.(5)Intaking antibiotics or probiotics within the past two weeks.(6)Intaking antianxiety, antidepressant, or other psychotropic drugs within the past month.(7)Need for long-term use of medications for diarrhoea.(8)History of severe diseases, such as myocardial infarction, cerebral infarction, and malignant tumour, judged by the investigators as disqualifying conditions.(9)Major mental illnesses, inability to control one's actions, or inability to cooperate.(10)Illiteracy, inability to understand the informed consent form, or inability to independently sign the informed consent form.

### Volunteer recruitment

2.4

The investigators recruit volunteers from the public via oral communication, posters, and dissemination of WeChat official account. With the help of WeChat, a two-dimensional (QR) code is available for volunteers to scan and register for enrolment, submitting demographic data, and answering questions related to inclusion and exclusion criteria. Then, the potentially eligible volunteers will undergo three rounds of screening, as follows.

First, the registration information is collected and collated, according to which potentially eligible candidates are invited to participate in a face-to-face consultation with clinicians and researchers for the further screening.

Second, a series of face-to-face consultations are organized: 1) Trained researchers introduce the trial to the potentially eligible volunteers through video and information sheets regarding the main aspects of the trial, especially the content of informed consent materials, and discuss the trial with the potentially eligible volunteers. 2) Then, the clinicians also have an informed face-to-face consultation with the potentially eligible volunteers to confirm the registered information, further selecting out potentially eligible volunteers according to inclusion and exclusion criteria to proceed in the next procedure. The selected potentially eligible volunteers are essential to sign an informed consent form directly with a member of data management team (DMT) before proceeding into the next procedure.

Third, the potentially eligible volunteers undergo a 14-day screening period. During the third round of selecting, the potentially eligible volunteers are not allowed to take any medicines or health products to improve their diarrhoea symptoms. And each volunteer will be asked to collect one stool sample and complete an online defecation diary (Appendix 2). At the end of the screening period, the diary and stool exam results will be reviewed and used to select eligible volunteers. Only then, the selected eligible volunteers can take part in the following formal intervention and follow-ups (Fig. 1).

### Randomization and blinding

2.5

Based on the order of registering during above recruitment, eligible volunteers are given a serially unique number, i.e., 001, 002, 003, 004, 005, and so on. The unique number is used as volunteer's identification card throughout the whole research periods instead of volunteer name or any other information, so as to guarantee confidentiality for volunteers. For each unique number, a random sequence is automatically generated using the computer software by two independent project administrators. The unique number with an odd random sequence is assigned into probiotic group, while the unique number with an even random sequence is assigned into placebo group. During the study, except two independent project administrators, the other participants of the study, including volunteers, treatment packs distributors, data collectors and analysts are blinded to the randomization sequence, namely the grouping. The randomization sequence is maintained by two independent project administrators and will only be unblinded in the case of major safety issues or when performing the interim or final data analysis. Moreover, the probiotics or placebo treatment packs are labelled with the foregoing unique numbers according to the grouping of the unique numbers, and the treatment packs distributors distribute the treatment packs according to the unique number on the packs to the corresponding volunteers, in such a way, allocation concealment is achieved.

### Study interventions

2.6

One probiotics or placebo powder pack per day. One probiotics powder pack contains 100 billion colony-forming units (CFU) of *L. plantarum* P9. *L. plantarum* P9 powder comprises *L. plantarum* P9 (40%), maltodextrin (20%), orange powder (20%), and maltitol (20%). The placebo comprises maltodextrin (60%), orange powder (20%), and maltitol (20%) and has the same appearance, packaging, and taste as the *L. plantarum* P9 powder. Both probiotics and placebo packs are stored in a 4 °C, dry place away from direct sunlight. At the end of the phase, all unused probiotics or placebo and used (empty) packs are collected, so as to calculate volunteers’ compliance.

The study is designed to include three phases, a period of screening (an observation period of pre-administrating), an observation period of administrating, and an observation period of post-administrating (Table 1). The interventions in each phase are as follows.(1)Period of screening (observation period of pre-administrating) (days −14 to 0): volunteers do not receive probiotics or placebo. Eligibility screening are performed as described in “volunteer recruitment part” (Table 1).(2)Observation period of administrating (days 0–28): 1) For probiotics group: volunteers take *L. plantarum* P9 powder with warm boiled water (below 40 °C) on a full stomach, 1 pack per day (i.e., 100 CFU/d); if volunteers have to take antibiotics during the administration, the probiotics is taken 2 h later. 2) For placebo group: volunteers take the placebo in the same manner as probiotics group.(3)Observation period of post-administrating (days 29–42): No interventions are taken during the study.

**Table 1 tbl1:** Study and follow up schedule.

Item		Period of screening (observation period of pre-administrating)		Observation period of administrating		Observation period of post-administrating
		Visit 0	Visit 1	Visit 2	Visit 3	Visit 4
		(Days −14 to −1)	Day 0	Day 14	Day 28	Day 42
Collection of volunteers' basic information		**✓**				
Screening		**✓**				
Informed consent form		**✓**				
Stool test (including occult blood)		**✓**				
Defecation diary		Completed Online Daily				
Primary outcomes	Diarrhoea severity score		**✓**	**✓**	**✓**	**✓**
Secondary outcomes	Weekly mean frequency of defecation		**✓**	**✓**	**✓**	**✓**
	Weekly mean stool appearance score		**✓**	**✓**	**✓**	**✓**
	Weekly mean stool urgency score		**✓**	**✓**	**✓**	**✓**
	Emotional state score		**✓**	**✓**	**✓**	**✓**
	Gut microbiome		**✓**		**✓**	**✓**
	Faecal metabolome		**✓**		**✓**	**✓**
Safety measures	Adverse events (AEs)			**✓**	**✓**	**✓**
	Serious adverse events (SAEs)			**✓**	**✓**	**✓**
Verification of compliance with the intervention					**✓**	
Special situations related to defecation (e.g., concomitant medications)			**✓**	**✓**	**✓**	**✓**

Note: The outcome measures, weekly mean frequency of defecation, weekly mean stool appearance score and weekly mean stool urgency score are calculated from the defecation diary. The defecation diary completed from day −14 to −1 will be used for volunteer selection and baseline data. The detection of gut microbiome will be conducted within 2 months after the end of follow-ups, and the detection of faecal metabolome will be implemented within 2 months when data analysis finds that the probiotics present significant effect on gut microbiome.

### Prohibited confounding interventions

2.7

The following interventions or factors may confound the results of the study and are prohibited: 1) other kinds of probiotics, prebiotics, and foods containing probiotics (such as yoghurt); 2) antianxiety, antidepressant, and other psychotropic drugs; 3) other substances may benefit intestinal symptoms. Furthermore, antibiotics are not advised, and normal dietary habits are recommended during the study. All concomitantly used substances/drugs related to defecation are required to record with an explanation via online daily diary (Appendix 2).

### Primary outcome

2.8

The primary outcome is the diarrhoea severity score, which is set as to the gastrointestinal symptom rating scale (GSRS) [[33], [34], [35], [36]]. The outcome measure is equal to the sum of mean defecation frequency score per day, mean stool consistency score per time, and mean stool urgency score per time within the past 7 days (see Appendix 2). The diarrhoea severity score will be assessed on days 0 (baseline), 14, 28, and 42. A higher score indicates more severe diarrhoea, Table 1. The details of calculation are as follows.

A defecation diary developed with reference to the literatures [33,34,37] will be completed daily online by the volunteers (Appendix 2). Based on the diary, the mean defecation frequency score per day, mean stool consistency score per time, and mean stool urgency score per time will be obtained. The defecation frequency score is ranked as: 0-point, one to two a day; 1-point, three to four times a day; 2-point, five to six times a day; 3-point, seven times a day or more frequently. The mean defecation frequency score per day is equal to “total defecation frequency score within the past 7 days/7”. The stool appearance score refers to Bristol stool type (Appendix 1) and must be recorded for each defecation: types 4–7 correspond to 0–3 points, respectively. The mean stool consistency score per time is equal to “total stool consistency scores within the past 7 days/total times”. The stool urgency score must be also recorded for each defecation: 0-point, no urgency; 1-point, a little urgency; 2-point, sudden need to have a defecation that must be addressed immediately; or 3-point, incontinence resulting in uncontrolled defecation and may stain pants. The mean stool urgency score per time is equal to “total stool urgency score within the past 7 days/total times”.

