Multidimensional outcomes are examined to produce a chain of evidence from causal improvements in metagenomic and metabolomic data to clinical symptoms and then to the emotional state. Chronic diarrhoea can disturb the patient's quality of life, work performance and wellbeing [10]; thereby, the relevant outcomes are chosen, including the diarrhoea severity score [33,34], weekly mean frequency of defecation, weekly mean stool appearance score [33,37], weekly mean stool urgency score [34], emotional state score [38] according to corresponding references [33,34,37,38]. The diarrhoea severity score is a comprehensive indicator calculated from weekly mean frequency of defecation, weekly mean stool appearance score, and weekly mean stool urgency score as described in “Primary outcome part”, so it is more reasonable to be the primary outcome than the left. Furthermore, both of inter- and intra-group differences will be analysed. In our opinion, the results of analysis are appropriate to present the effect of *L. plantarum* P9 on defecation and quality of life in individuals with chronic diarrhoea. Moreover, the study will try to explore the possible action modes of probiotics to improve chronic diarrhoea, from the aspects of gut microbiome and faecal metabolome. Gut microbiome has been found to be altered in chronic diarrhoea patients and may be a cause of chronic diarrhoea [12]. Probiotics are live organisms that when administered in adequate amounts confer health benefits to the host and improve the gut microbial balance [[13], [14], [15], [16], [17],^26^]. The detection of gut microbiome and faecal metabolome would provide an explanation for the efficacy of *L. plantarum* P9 on chronic diarrhoea. Thus, the set of multidimensional outcomes will form a chain of evidence.

A limitation is the way of follow up in this study (completing diary online daily), which may lead to bias about the effectiveness of probiotics. To overcome the limitation, a WeChat group is established for the cohort of volunteers, so the researcher can timely post messages via the WeChat group, keeping a good compliance; and an DMT is formed to promptly assess the study quality and safety. during the assessment, once an uncertainty about the data arises, the DMT can urge the data collectors to resolve it. The confounding factors are also prohibited. In such a way, the bias would be minimized as far as possible.

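### The frequency part of the primary score is divided by a fixed 7, so if an incomplete diary week is scored as written, each unrecorded day counts as 0 points

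*Protocol article*

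**What the plan says.** Section 2.8 (Primary outcome) builds the diarrhoea severity score from three parts, all taken from a daily online diary over the preceding week and assessed on days 0, 14, 28 and 42. A higher total is worse.

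- **Frequency.** Each day is given 0 to 3 points. The scale begins "0-point, one to two a day; 1-point, three to four times a day" and ends at "3-point, seven times a day or more frequently". The weekly value is "total defecation frequency score within the past 7 days/7".
- **Consistency.** Each stool is given 0 to 3 points, and the weekly value is "total stool consistency scores within the past 7 days/total times".
- **Urgency.** Each stool is given 0 to 3 points, and the weekly value is "total stool urgency score within the past 7 days/total times".

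The article gives no minimum number of diary days, no rule for a day without an entry and no other divisor. Section 2.12 plans reminders to fill in the diary, and section 2.14 has the data management team query doubtful data. The Discussion concedes a weakness here: "A limitation is the way of follow up in this study (completing diary online daily"), and adds that this may bias the estimate of effectiveness.

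**The concern.** One missing day is handled in two different ways within the same composite. For consistency and urgency it drops out of both numerator and divisor. For frequency it drops out of the numerator only, so a blank day cannot be told from a day scored "0-point, one to two a day". The scale has no separate place for a day without stools, so a stool-free day and an unrecorded day also give the same value.

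The resulting score looks complete. A missing-data method applied later to the weekly scores would find nothing missing in that week. Three things are at stake:

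- a true difference in the frequency component is diluted when both arms miss days;
- less diary-keeping over the course of the study can pass for improvement in the within-group comparisons of days 0, 14, 28 and 42 in section 2.15;
- if completion differed by arm, the primary comparison would be biased.

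**Working it through.** **Inputs from section 2.8.** Divisor 7 for frequency; recorded stools as divisor for consistency and urgency; each component 0 to 3, so the total runs from 0 to 9. The article gives no completion rate and no mean frequency score, so the values of s, m, p and the mean below are illustrative. It also states no figure on this point that could be reproduced. For a complete week the formula is the correct daily mean.

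**Step 1: one volunteer, constant daily score s, m unrecorded days.**

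As written: s(7 − m)/7. Divided by recorded days: s(7 − m)/(7 − m) = s. Shortfall: s·m/7.

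| s | m = 1 | m = 2 | m = 3 | shortfall per missed day |
|---|---|---|---|---|
| 0 | 0 | 0 | 0 | 0 |
| 1 | 0.86 | 0.71 | 0.57 | 1/7 = 0.14 |
| 2 | 1.71 | 1.43 | 1.14 | 2/7 = 0.29 |
| 3 | 2.57 | 2.14 | 1.71 | 3/7 = 0.43 |

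In general, the value as written is never above the recorded-days value. When days are missing, it is lower whenever any recorded day scores above 0.

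**Step 2: effect on the total, with two of seven days unrecorded.**

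| Week | Full diary | As written | Recorded-days divisor |
|---|---|---|---|
| (a) 5 stools daily, consistency 2, urgency 1; any two days lost | 2.00 + 2.00 + 1.00 = 5.00 | 1.43 + 2.00 + 1.00 = 4.43 | 2.00 + 2.00 + 1.00 = 5.00 |
| (b) five days of 5 stools (consistency 2, urgency 2), two days of 2 stools (0, 0); the two mild days lost | 1.43 + 1.72 + 1.72 = 4.88 | 1.43 + 2.00 + 2.00 = 5.43 | 2.00 + 2.00 + 2.00 = 6.00 |
| (c) five days of 3 stools (1, 1), two days of 7 stools (3, 2); the two bad days lost | 1.57 + 1.97 + 1.48 = 5.02 | 0.71 + 1.00 + 1.00 = 2.71 | 1.00 + 1.00 + 1.00 = 3.00 |

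(Sums are taken before rounding.) Week (a) isolates the effect of the divisor. In week (b) the frequency part is unchanged, because the lost days would have scored 0, and the total rises because the other two parts lose mild stools. In week (c) most of the fall comes from which days were lost, not from the divisor. Weeks (b) and (c) also show that a recorded-days divisor does not cure selective missingness.

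**Step 3: group level.** If a fraction p of days is missing regardless of severity, the expected frequency component is (1 − p) × its mean.

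- Same p in both arms: a true difference in this component is multiplied by (1 − p). At p = 0.20 it keeps 80% of its size.
- Completion falling over time: at an assumed mean of 1.5, going from 0% to 20% missing lowers the component by 1.5 × 0.20 = 0.30 with no clinical change.
- Different p by arm, no true difference, assumed mean 1.5: 10% v 20% gives 1.5 × (0.90 − 0.80) = 0.15 points; 10% v 30% gives 1.5 × (0.90 − 0.70) = 0.30 points.

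**Step 4: yardstick.** Against the 3-point difference planned in section 2.13, the last two figures are 0.15/3 = 5% and 0.30/3 = 10%. That comparison gives limited reassurance. A score confined to 0 to 9 cannot have a standard deviation above about 9/2 = 4.5, yet section 2.13 assumes 6.8, so the planning figures do not fit the score as defined here.

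**The case against.** The strongest reply is that the formula was written for a complete week. The diary is meant to be filled in every day, and for seven recorded days a divisor of 7 is right. The article nowhere says that a blank is entered as 0, or that an incomplete week is scored at all. A rule for incomplete weeks is normal content for an analysis plan or scoring manual, and Appendix 2, to which section 2.8 refers, is not shown. It is therefore fair to say that the protocol does not prescribe blank-as-zero, and an unseen document may set a completeness rule. What remains is that the article prints an explicit calculation for the primary outcome. Used as printed on an incomplete week, it has this effect, while the two sister components do not.

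The safeguards deserve mention: reminders, data queries, a payment for finishing follow-up, and a main dataset of those who finished it. They should reduce missed entries. None of them changes the divisor, and the compliance subgroups are based on empty packs, not on diaries.

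A reader might infer that every missed day lowers the score. The documents do not support that: a missed day with one or two stools leaves the frequency part alone, the eligibility criteria set no minimum stool frequency, and the total can rise, as in week (b). A reader might also infer that the treatment comparison is biased. That needs completion to differ by arm. Volunteers and data collectors are blinded, and nothing in the article points to such a gap.

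Finally, the fixed 7 does handle genuine stool-free days sensibly. Dividing by recorded days would drop them and inflate the score unless they can be told apart from blanks. That objection stands and shapes the fix.

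**Conclusion.** The point holds as a conditional one. If the section 2.8 formula is applied to weeks with unrecorded days, each such day counts as 0 points in the frequency component. The shortfall against a recorded-days divisor is s/7 per missed day: 0.14, 0.29 or 0.43 points for a constant daily score of 1, 2 or 3, on a total of 0 to 9. Dilution with equal non-completion, and apparent within-group improvement with falling completion, follow from the formula once days are missed. Between-arm bias is possible only with unequal completion. The figures of 0.15 and 0.30 points rest on an assumed mean of 1.5 and assumed missing fractions, since the article gives neither.

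This should be corrected before unblinding. It does not rank as a flaw that must be removed for the trial to be interpretable: it affects one of three components, only in incomplete weeks, by an amount that the documents do not let anyone determine.

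**What to change.** In section 2.8 and the scoring code, define the mean daily frequency score as the total frequency score divided by the number of days with a completed diary. Count a confirmed stool-free day as a completed day with 0 points. Before unblinding, set a minimum number of completed days for a week to be evaluable (4 of 7 is one example, not a figure from the documents), and treat weeks below it as missing under whatever missing-data method applies.

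This takes about a sentence of text and a line of code. It works only if stool-free days can be distinguished from unrecorded ones. If the diary does not already allow such an entry, adding one helps only the diaries still to be completed, and section 4 reports 174 volunteers already enrolled. The other costs are that some weeks become missing and that the average assumes missed days resemble recorded ones.
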